## Methods/design

### Study design

We are conducting a two-arm, cluster-randomized, open-label controlled trial of MMP with t3-day DHA-PIP and weekly PQ compared to focused screening and treating (FSAT) following current national treatment guidelines. Participants in the MMP arm receive a monthly 3-day course of fixed-combination tablet containing 40 mg of dihydroartemisinin and 320 mg of piperaquine phosphate for three consecutive months. Those aged 13 years and older receive low-dose weekly PQ (22.5 mg) therapy to prevent malaria transmission for 12 weeks. Participants in the FSAT arm are screened with highly sensitive polymerase chain reaction (PCR) methods, and all those testing positive for malaria receive therapy with first-line antimalarials following current national treatment guidelines. At the time of protocol development, artesunate-mefloquine combination therapy is the first-line treatment for *P. falciparum* in provinces with known antimalarial resistance, with a single, low dose of PQ (15 mg) to prevent malaria transmission. For participants in the FSAT arm with *Plasmodium vivax* malaria, the recommended treatment for asexual parasitemia is DHA-PIP. All patients with *P. vivax* in the FSAT arm receive treatment with 15 mg of PQ daily for 14 days if G6PD normal, or 45 mg weekly if G6PD deficient.

### Study site and population

The study takes place at multiple military encampments in malaria-endemic areas in border areas authorized by the Ministry of National Defense. Sites were chosen based on current malaria incidence estimates by the RCAF health services in consultation with the National Center for Parasitology, Entomology, and Malaria Control (CNM) in Cambodia and the Armed Forces Research Institute of Medical Sciences (AFRIMS). For reasons of operational security, locations or other descriptors will not be further described here. All sites will be evaluated as simultaneously as feasibly possible.

Military volunteers aged 18–65 years of age and their dependents of ≥ 2 years of age, eligible for care at an RCAF facility, or otherwise eligible Cambodian civilians at risk for contracting malaria who live within close proximity, are enrolled if they meet the following criteria: are able to give informed consent/assent; reside in the selected study areas; are available for monthly follow-up for 6 months; agree not to seek outside medical care for febrile illness unless referred by study team; and are authorized by respective military unit commanders to participate in the study if on active duty. Volunteers who have known allergy or other contraindication to study medication; are pregnant, lactating or are women of childbearing age who do not agree to use an acceptable form of contraception during the study; or are judged by the investigator to be otherwise unsuitable for study participation are excluded from the study.

### Cluster randomization, allocation, and blinding

Geographical areas were randomized prior to study start to a 1:1 allocation of MMP or FSAT using time- and region-blocked randomization to ensure that randomization is geographically distinct, and that malaria incidence is evenly distributed among groups given that high and low transmission areas exist. Volunteers meeting the enrollment criteria receive permethrin- or sham-treated (water-treated) uniforms according to their cluster’s assignment in single-blind fashion (volunteer blinded to assignment but not investigator). Entomology staff conducting uniform testing are also blinded to treatment. Diagnostic microscopists are blinded to each others’ readings and to study arm assignment. There is otherwise no blinding during the study.

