### Aim and objectives

We present a pilot operational research protocol to investigate the effectiveness of monthly prophylactic drug administration compared to a focused screen-and-treat approach to inform a regional malaria elimination initiative by the Royal Cambodian Armed Forces (RCAF).*Primary objective*: to compare the effectiveness of focused screening and treatment (FSAT) following current national treatment guidelines versus monthly malaria prophylaxis (MMP) with dihydroartemisinin-piperaquine (DHA-PIP) in combination with weekly primaquine (PQ) (22.5 mg) as transmission-blocking and radical curative agent to reduce the risk of malaria infection in personnel residing in military encampments on the Thai-Cambodian border*Secondary objectives*:◦ To estimate the incremental benefit of wearing a permethrin insecticide-treated uniform (ITU) over drug therapy and existing vector control interventions compared to a sham insecticide-treated uniform (sITU) treated with water. Civilian participants will have comparable selected outer garments treated◦ To define the proportion of asymptomatic carriers of malaria in the population, including the cumulative incidence and incidence density of microscopic and submicroscopic blood-stage parasitemia and gametocytemia◦ Additional secondary objectives can be found in Table 1/Additional file 1

**Table 1 Tab1:** Outcomes

Objectives	Outcomes/endpoints
Primary	
To compare the effectiveness of focused screening and treatment (FSAT) following current national treatment guidelines versus targeted monthly malaria prophylaxis (MMP) with DHA-piperaquine in combination with low-dose weekly primaquine (PQ) (22.5 mg) for 12 weeks	Absolute risk reduction in a cluster based on those individuals’ polymerase chain reaction (PCR)-corrected absence of parasitemia at the end of 6 months in the MMP versus FSAT clusters
Secondary	
Estimate the incremental benefit of insecticide-treated uniforms (ITU) over drug therapy and existing vector control interventions compared to a sham insecticide-treated uniform (sITU)^a^	Absolute risk reduction in a cluster based on those individuals’ PCR-corrected absence of parasitemia at the end of 6 months^a^ Proportional landings of mosquitoes on treated uniform’s swatch side of cages

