#### PCR genotyping

One milliliter of blood is drawn on day 1 if malaria-positive and at recurrence. PCR genotyping of *msp1*, *msp2*, and *GLURP* genes is performed to identify the unique fingerprint of the infecting parasite and any subsequent development of malaria after therapy in order to determine if it is a recrudescent infection or new infecting genotype [22]. Gametocyte PCR and molecular marker analysis is performed as previously described [23–26].

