### Statistical methods

The primary study endpoint will be the absolute risk reduction (ARR) with 95% confidence intervals (CIs) based on the proportion of volunteers in each arm with absence of PCR-positive parasitemia at the end of 6 months using an intention-to-treat analysis (Table 1). In addition, logistic regression modeling may be employed to provide multivariate analyses based on other possible study confounders such as age, proportion of children, proportion of pregnant women, etc. The primary study population will be intention-to-treat, defined as all volunteers (both military and civilian family members) who are enrolled at either site. The per-protocol analysis population will include all those volunteers who enrolled and completed follow-up up to 180 days. However, volunteers lost to follow-up that do not complete up to 180 days of follow-up will be excluded from the per-protocol analysis, but included in an intention-to-treat analysis.

Secondary study endpoints are pilot endpoints to include incidence rates, molecular and parasitological endpoints, safety, vector control effectiveness (e.g., permethrin-treated versus water-treated uniforms), and comparison of malaria and G6PD diagnostic modalities. The calculation of incidence rates (attack rate over total time at risk) for prophylactic and FSAT groups will be calculated adjusted and unadjusted with 95% CI. All volunteers completing at least one follow-up assessment will be included in the safety analysis. The safety analysis database will include those volunteers in the set of randomized volunteers who receive at least one dose of study drug. All parasitological data will be included in the parasitological analyses. A stratified analysis comparing the vector control arms within each group will also be compared as those remaining malaria-free at 180 days. Given the possibility of the highly variable nature of transmission at the geographical sites, existing pre-enrollment malaria surveillance data by RCAF and day 1 screening data by AFRIMS will guide if a pair-matched analysis is necessary.

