### Data storage and handling

Clinical and laboratory data pertaining to drug efficacy are collected and managed by AFRIMS Immunology and Medicine staff and RCAF personnel. All data and medical information obtained from study volunteers are considered privileged and confidential. Volunteers enrolling in the study are issued a unique identification code (UIC), which is used on all study files and clinical sample labels. Individually identifiable volunteer information other than the UIC are not transcribed on other study documents to include laboratory sample labels, case report forms, nor included in the presentation of study results. Data is double-entered into a Microsoft Access database (Microsoft Corp) with source data verification for each entry.

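### As written, the plan masks smear readers to study arm but not the PCR readers, whose result decides the primary endpoint

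*Protocol article*

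**What the plan says.** The trial is a "two-arm, cluster-randomized, open-label controlled trial". The protocol article's section on cluster randomization, allocation and blinding names three masked groups:

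- volunteers, to permethrin or sham treatment of clothing only;
- entomology staff who test the uniforms;
- diagnostic microscopists, to each other's readings and to study arm.

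It then ends: "There is otherwise no blinding during the study".

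Under Laboratory procedures, the Microscopy subsection repeats the masking for smear reading. It gives none for the real-time PCR described in the same subsection, and the PCR genotyping subsection gives none either.

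Statistical methods bases the primary absolute risk reduction on "the proportion of volunteers in each arm with absence of PCR-positive parasitemia at the end of 6 months". Table 1 words the endpoint as "PCR)-corrected absence of parasitemia at the end of 6 months in the MMP versus FSAT clusters" (the stray bracket closes a spelled-out abbreviation). Genotyping is done "to determine if it is a recrudescent infection or new infecting genotype".

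Data storage and handling gives each volunteer a unique code, "which is used on all study files and clinical sample labels". It does so in the context of privacy.

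**The concern.** Participants and field staff cannot be masked to a comparison of monthly prophylaxis with screening and treatment. Masking whoever determines the outcome is therefore the main safeguard left against assessment bias. The plan gives it to smear reading and, by its closing sentence, withholds it from the PCR, the assay on which the primary endpoint is defined.

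Real-time PCR is instrument-read, but some judgement remains: whether a weak late signal is positive, and whether a sample is run again. If staff know the arm, these decisions can differ between arms. Such errors do not average out. They pass directly into the absolute risk reduction.

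**Working it through.** **Who is masked, against who decides the endpoint**

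| Reading | Masked to arm? | Role |
|---|---|---|
| Uniform swatches (entomology) | Yes, to uniform treatment | Secondary |
| Blood smears | Yes | Diagnosis; confirmed by PCR |
| Real-time PCR | None stated; the closing sentence excludes it | Primary endpoint |
| Genotyping | None stated; the closing sentence excludes it | Recurrence classification; role in the primary endpoint unclear |

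The list of masked groups is closed, so the gap comes from a stated rule and not only from silence in a condensed article.

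**Can the arm be inferred from a coded sample?** There are eight clusters of 80 to 140 volunteers, each allocated as a whole. Anyone who knows a sample's encampment and the allocation knows the arm of everyone in that cluster. The article does not say whether the code or the shipment reveals the encampment. Masking in practice is therefore undetermined; it is not shown to be absent.

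**Do the arms give different reasons to repeat a test?** In the first 3 months, a PCR-only positive leads to treatment under FSAT, whereas a symptom-free MMP volunteer continues study treatment (Treatment intervention). In the last 3 months both arms follow national guidelines. This asymmetry therefore bears on the early visits more than on the month-6 reading.

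**Size of a possible bias.** The plan contains no figure to reproduce on this point. As an illustration, let pM and pF be the true malaria-free proportions under MMP and FSAT, fnM the share of MMP positives read as negative, and fpF the share of FSAT negatives read as positive:

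observed ARR = [pM + (1 − pM) × fnM] − pF × (1 − fpF)

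Inputs from Sample size rationale: pF = 0.50, and pM = 1.00 (incidence reduced to zero). A second case takes pM = 0.90 as an assumption; the same section cites models that put prevalence below 10% after multi-round mass treatment. The misreading rates are assumptions, since the documents give none, and both are set in the direction that favours MMP.

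| pM | fnM | fpF | True ARR (points) | Observed ARR (points) | Shift (points) |
|---|---|---|---|---|---|
| 1.00 | any | 0.05 | 50 | 100 − 47.5 = 52.5 | 2.5 |
| 0.90 | 0.05 | 0 | 40 | 90.5 − 50 = 40.5 | 0.5 |
| 0.90 | 0.20 | 0 | 40 | 92 − 50 = 42.0 | 2.0 |
| 0.90 | 0.05 | 0.05 | 40 | 90.5 − 47.5 = 43.0 | 3.0 |
| 0.90 | 0.20 | 0.05 | 40 | 92 − 47.5 = 44.5 | 4.5 |

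The shift runs from 0.5 to 4.5 points. In relative terms that is 0.5/40 = 1.25% to 4.5/40 = 11.25% of the true difference.

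**The case against.** The case against has several parts, and some of it stands.

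- **The PCR laboratory is never named as unmasked.** This is true. The reading rests on one general sentence, and coded labels may already hide the arm. That limits the point to what the plan states. It does not remove it, because the sentence rules out other masking and the code is presented only as a privacy measure.
- **Genotyping may not enter the primary endpoint.** This stands. A reader might infer from Table 1's PCR-corrected wording that genotype matching decides the primary result. The documents do not establish that: Statistical methods counts plain PCR positivity, the Microscopy subsection uses PCR correction to mean confirmation of smears, and PCR-corrected *P. falciparum* recrudescence is listed as a secondary endpoint. If Table 1 has the smear-confirmation sense, the masked smear is also an input to the endpoint.
- **A large distortion is not shown.** One could take about 500 volunteers per arm (half of roughly 1000) and suppose five borderline samples per arm misread in opposite directions. The shift is then 10/500 = 2 points, or 2/5 = 40% of a 5-point difference. Both the misreadings and the 5-point difference are assumptions. Against the 40 to 50 points above, the same shift is 4 to 5% (2/50 to 2/40).
- **Masking is not shown to be free of cost.** No section addresses this. PCR results trigger treatment in the FSAT arm, encampments are separate, and sites are evaluated only as close in time as is feasible. Insisting on plates that mix arms could hold up results.
- **Cut-offs, repeat rules and plate layout are laboratory detail.** This stands. An article may leave them out, and their absence is not criticised here.

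**Conclusion.** The point holds in a limited form. The plan masks smear readers to arm and, by its own closing sentence, does not mask the readers of the PCR that defines the primary endpoint. Nothing else in the article contradicts this, and the coded labels are not said to conceal arm or cluster. The Limitations section lists compromises accepted for field conditions, and this is not among them.

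The likely effect is modest: about 0.5 to 4.5 points in the illustration, against a true difference of 40 to 50 points. That range rests on assumed misreading rates of 5 to 20% in MMP positives and 5% in FSAT negatives, all in one direction. It would matter relatively more if the true difference were small. The documents do not show that biased reading will occur, or that it could overturn a difference of the planned size. This is a cheap improvement, not a flaw that undermines the design.

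**What to change.** Amend the end of the section on cluster randomization, allocation and blinding to state that:

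1. real-time PCR, and genotyping if it is used for the endpoint, is read on coded samples by staff who know neither arm nor cluster;
2. the same positivity and repeat rule applies to both arms;
3. results return to the clinic by study code.

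Mix samples from both arms on a plate only where this does not delay results needed for treatment. If the coding already masks the laboratory, it is enough to correct the closing sentence and say how cluster identity is hidden.

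The cost is a short text change and some laboratory handling to keep the allocation list and encampment identity away from PCR readers. Samples are already coded, so the burden should be small, although the documents do not quantify it.

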### Treatment intervention

Volunteers randomized to MMP arm aged 13 years and older receive a monthly 3-day treatment course of (DHA-PIP; 360/2880 mg) for 3 months. They will also receive a weekly dose of 22.5 mg of PQ for 12 weeks. Children of 12 years of age or less will receive only a monthly 3-day weight-based treatment dose of DP for 3 months without PQ treatment. In the MMP arm, symptomatic patients or microscopy-confirmed parasitemia in the first 3 months are considered a failure of prophylaxis and treatment is given according to the national treatment guidelines. If the volunteer has parasitemia detectable by PCR only and is symptom free at monthly follow-up, the study treatment with monthly DHA-PIP is continued for 3 months as outlined for the MMP arm. To reduce phlebotomy requirements for G6PD testing and potential hemolytic risk in children, PQ is not be administered to those less than 13 years old.

Volunteers randomized to the focused screening and treatment (FSAT) arm are treated according to current national malaria treatment guidelines if they test positive for malaria based on blood smear and/or real-time PCR results during monthly follow-up. In the FSAT arm, all volunteers with parasitemia detectable with PCR receive antimalarial treatment, even if they are symptom- free.

At the time of protocol development, national treatment guidelines for areas of known piperaquine resistance, to include the designated study regions, recommended a 3-day course of artesunate and mefloquine (A + M) and a single 15-mg dose of PQ for acute *P. falciparum*, or DP for blood-stage *P. vivax* infection. Elimination interventions are carried out monthly during the first 3 months after enrollment, and then followed by 3 months of additional malaria assessment by smear and PCR diagnosis with malaria treatment as necessary following current national treatment guidelines (Fig. 1, Table 2, Fig. 2). Those febrile but negative for malaria are referred for evaluation and treatment of alternative diagnoses.

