**Fig. 1 Fig1:**
[figure not shown]
Study flow diagram

**Table 2 Tab2:** Table of times and events for adults and children over 12 years of age

Event	Screen/enroll day 1	Day 3^3^	Day 30^7^	Day 60^7^	Day 90^7^	Day 120^7^	Day 150^7^	Day 180^7^	Malaria diagnosis/ recurrence^2^
a. Informed consent	X								
b. Medical history	X								
c. Physical exam	X								X
d. Brief clinical evaluation and vital signs^1^			X	X	X	X	X	X	X
e. Malaria RDT, DBS, smear and PCR genotyping^6^	2 mL		1.5	1.5	1.5	1.5	1.5	1.5	1.5 mL
i. CBC	1 mL	1 mL^3^							
k. Molecular resistance markers^2^									6 mL
l. G6PD RDT, fluorescent spot, quantitative testing	1.5 mL								
m. Gametocyte PCR	2.5 mL		2.5	2.5	2.5	2.5	2.5	2.5	2.5 mL
n. Urine pregnancy test (women of child-bearing age)	X		X	X					X
o. Malaria treatment^4,5^	X		X	X					X
Daily phlebotomy (mL)	7	1^3^	4	4	4	4	4	4	10
Cumulative phlebotomy (approximately mL)	7		11	15	19	23	27	31	41

^1^Brief clinical evaluation includes an interval medical history, vital signs and a directed physical exam as indicated

^2^Performed only for volunteers with smear-positive malaria. Those with PCR-positive malaria will be treated following national guidelines but will not have blood drawn for molecular markers of resistance

^3^To be drawn for G6PD-deficient volunteers only. All G6PD-deficient volunteers with > 10% of Hgb or HTC drop on D3 will have CBC on day 7

^4^Patients screening positive on microscopy and/or PCR for *P. falciparum* malaria in the FSAT arm will receive currently recommended blood-stage antimalarials under published national treatment guidelines as well as single, low-dose primaquine (15 mg). Volunteers with *P. vivax* will be treated with the currently recommended blood-stage agent (DHA-PIP), as well as primaquine – G6PD-normal volunteers will receive 15 mg daily for 14 days, while G6PD-deficient volunteer will receive 45 mg × 8 weeks. All volunteers in the MMP arm will receive a fixed-dose 3-day course of DHA-piperaquine at 0, 24 and 48 h starting on days 1, 30, and 60, and a weekly 22.5-mg dose of primaquine for 12 weeks. All therapy will be directly observed

^5^For all volunteers with recurrent malaria, rescue therapy will be with the recommended agent(s) per national guidelines

^6^May be repeated as medically indicated (e.g., if patient is malaria-positive or otherwise ill on enrollment). An additional 0.5 mL will be collected on the day of enrollment for baseline G6PD genotyping

^7^Time window of ± 7 days

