**Fig. 2. Fig2:**
[figure not shown]
Study timeline for monthly malaria prophylaxis (MMP) intervention clusters. *Treat with artesunate and mefloquine. *DHA-PIP* dihydroartemisinin-piperaquine, *GC* gametocyte, *RDT* rapid diagnostic test, *PCR* polymerase chain reaction, *G6PD* glucose-6-phosphatase dehydrogenase, *CBC* complete blood count

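### The Treatment intervention section and Table 2 footnotes 2 and 4 give conflicting treatment rules for parasite-positive volunteers in the MMP arm

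*Protocol article*

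**What the plan says.** The Treatment intervention section of the protocol article splits positive MMP volunteers into two groups that do not overlap.

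- **Symptomatic or smear-positive:** the two are handled alike, and the sentence reads in part "microscopy-confirmed parasitemia in the first 3 months are considered a failure of prophylaxis and treatment is given according to the national treatment guidelines".
- **Positive by PCR only and symptom-free at a monthly visit:** "the study treatment with monthly DHA-PIP is continued for 3 months as outlined for the MMP arm".

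Table 2 covers both arms, for volunteers over 12 years of age. Three of its footnotes bear on the same people.

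- **Footnote 2** is attached to the malaria diagnosis/recurrence column and to the resistance-marker row. It says "Those with PCR-positive malaria will be treated following national guidelines but will not have blood drawn for molecular markers of resistance" and names no arm.
- **Footnote 4** says "All volunteers in the MMP arm will receive a fixed-dose 3-day course of DHA-piperaquine", starting on days 1, 30 and 60, "and a weekly 22.5-mg dose of primaquine for 12 weeks". It makes no exception for a volunteer who has failed. Its P. falciparum sentence is limited to the FSAT arm. Its P. vivax sentence, which sets a primaquine course by G6PD status, names no arm.
- **Footnote 5** sends all recurrent malaria to the agents in the national guidelines.

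Study design and Treatment intervention give the national guideline for P. falciparum as artesunate-mefloquine with a single 15 mg primaquine dose, and the blood-stage treatment for P. vivax as DHA-PIP. Study design states the P. vivax primaquine course for the FSAT arm.

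**The concern.** Staff at an encampment cannot follow all of these rules for one infected MMP volunteer. Two things are at stake.

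**Safety.** Volunteers with severe G6PD deficiency are enrolled (G6PD testing), and the protocol has a halting rule for hemolysis after primaquine. The text should therefore not leave open whether a treatment course replaces scheduled MMP dosing or is added to it.

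**What the MMP arm is.** The treatment that infected MMP volunteers receive is part of the strategy under test. It can affect PCR status at 6 months, P. vivax recurrence and the safety comparison of 12 against 8 weeks of primaquine. Eight encampments allocated 1:1 give four per arm. If encampments resolved the conflict differently, so few clusters would not average the difference out. Nothing in the article shows that they do.

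**Working it through.** The plan states no figure on this point, so the check sets the rules side by side and then does arithmetic on the stated primaquine doses.

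**Step 1. Rules by type of MMP volunteer**

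| MMP volunteer | Treatment intervention | Table 2 | Result |
|---|---|---|---|
| PCR only, no symptoms, P. falciparum | Continue monthly DHA-PIP | Footnote 2: national guidelines, i.e. artesunate-mefloquine plus primaquine 15 mg | Contradiction |
| PCR only, no symptoms, P. vivax | Continue monthly DHA-PIP | Footnote 2: national guidelines, with DHA-PIP as blood-stage drug | Same blood-stage drug; primaquine unclear |
| Symptomatic or smear-positive, P. falciparum | National guidelines: artesunate-mefloquine plus primaquine 15 mg | Footnote 4: all scheduled DHA-PIP courses and all weekly primaquine | Contradiction, or overlap if both are followed |
| Symptomatic or smear-positive, P. vivax | National guidelines, with DHA-PIP as blood-stage drug | Footnote 4: all scheduled MMP dosing, plus a P. vivax primaquine course with no arm named | Same blood-stage drug; two primaquine instructions |

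**Step 2. Timing.** Table 2 schedules malaria testing on days 1, 30, 60, 90, 120, 150 and 180. Footnote 4 starts MMP courses on days 1, 30 and 60. A positive result at any of those three visits belongs to a visit at which an MMP course is due. No sentence says whether that course is replaced, paused or continued.

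**Step 3. What literal overlap would mean for primaquine (age 13 and over)**

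Inputs: MMP 22.5 mg weekly for 12 weeks; P. falciparum single 15 mg; P. vivax 15 mg daily for 14 days if G6PD normal, or 45 mg for 8 weeks if deficient (Table 2 footnote 4; Study design gives the 45 mg as weekly).

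- MMP as planned: 12 × 22.5 = 270 mg
- P. vivax course, G6PD normal: 14 × 15 = 210 mg
- P. vivax course, G6PD deficient: 8 × 45 = 360 mg

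Total = MMP course + treatment course for one episode:

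- P. falciparum: 270 + 15 = 285 mg
- P. vivax, G6PD normal: 270 + 210 = 480 mg (480 / 270 = 1.8 times the plan)
- P. vivax, G6PD deficient: 270 + 360 = 630 mg (630 / 270 = 2.3 times the plan)

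The P. vivax totals need two assumptions together: that all 12 weekly doses continue, and that the full P. vivax course is added. They show what the wording fails to exclude, not what it instructs.

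**The case against.** The best defence is that Treatment intervention is coherent on its own. Its two branches cover different volunteers, and footnote 5 agrees with the first. Footnote 4 can be read as the default schedule in a times-and-events table, with the text as the specific rule for positives. Footnote 2 is mainly about who has blood drawn for resistance markers. Silence on stopping MMP dosing could be detail that an article leaves to the full protocol.

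Much of this stands. It does not remove the conflict, because footnotes 2 and 4 are stated rules. One covers PCR-positive malaria with no limit by arm, and the other covers every volunteer in the MMP arm. Nothing gives the text precedence over the table.

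Three stronger readings are tempting, but the documents do not support them.

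- **Fig. 2 sets a third, separate rule.** Its legend says "Treat with artesunate and mefloquine" without naming a species. For P. falciparum that is the stated national guideline. The figure cannot be seen here, so what the asterisk marks is unknown.
- **The protocol orders both regimens together.** No passage does. Study design ties the P. vivax primaquine course to FSAT, and the P. vivax blood-stage drug is DHA-PIP either way.
- **Infections present on day 1 count as prophylaxis failures and bias the result against MMP.** The first-3-months wording does not except day 1, but the failure label enters no listed endpoint. The primary endpoint is absence of PCR-positive parasitemia at 6 months.

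**Conclusion.** The point holds as two contradictions in current text. For a symptom-free MMP volunteer positive by PCR alone, Treatment intervention and Table 2 footnote 2 disagree, clearly so for P. falciparum. For a symptomatic or smear-positive MMP volunteer, Treatment intervention orders guideline treatment, while footnote 4 keeps all MMP dosing in place without exception and carries a P. vivax primaquine instruction limited to no arm.

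Overlapping regimens are not excluded. The 480 mg and 630 mg totals, against 270 mg planned, are hypothetical upper bounds for a single P. vivax episode under the two assumptions shown. No trial figure changes, and no bias in the primary endpoint is shown. The correction is still needed because it concerns treatment instructions in a population that includes severely G6PD-deficient volunteers, and because it settles what the MMP strategy consists of.

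**What to change.** Reconcile Treatment intervention with Table 2 footnotes 2 and 4 so that one rule applies to MMP volunteers by mode of detection (symptomatic, smear-positive, PCR only) and by species. The rule should:

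- say what happens to scheduled DHA-PIP and weekly primaquine when guideline treatment is given;
- say which arm or arms footnote 2 and the P. vivax sentence of footnote 4 apply to.

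Check the Fig. 2 legend against the agreed rule. The trial's clinical team decides the content; this review takes no view on which regimen is right.

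The cost is a wording amendment, with no extra volunteers, visits or tests.
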